## STUDY OBJECTIVES

The primary outcome of this study is to determine if ziprasidone is effective for the depressive mixed state in bipolar and unipolar depression.

1. **STUDY DESIGN**

This will be a four-site, block randomized (1:1 ratio) double-blind, placebo-controlled prospective study in which 100 patients will be enrolled. Patients will be randomized to ziprasidone or placebo in the 6 week acute phase of the study. Randomization will be stratified by three factors: subtype of depressive disorder (bipolar type II vs. unipolar), presence or absence of rapid cycling and duration of current MDE (< vs. > 3 months). The primary outcome measure will be change from baseline Montgomery-Asberg Depression Rating Scale scores in the acute phase. Enrollment will occur over 12 months.

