##### STUDY PROCEDURES

### Blinding and Controls

The study will be double blind and randomized. There will be two arms, ziprasidone and placebo, that will serve as comparators. All subjects will be offered the option of an open label courtesy trial of up to 8 weeks of treatment with ziprasidone at no charge upon their study conclusion. Subjects who do not complete the full 6-week double-blind trial will be eligible for the open courtesy trial after the baseline visit, given that they have been found eligible based on the inclusion and exclusion criteria.

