### Visit-Specific Treatment and Evaluation Sequence

Visits will be planned to occur at the screening visit and weeks 0, 1, 2, 3, 4, 5, 6. Research scales will be administered at each visit. For a detailed description of which scales are administered per visit, please see “XIV. Study Visit Schedule” on page 21. No research procedures will be performed without a patient first signing an informed consent. Laboratory tests, consisting of CBC with differential, biochemistry profile, ECG and urine pregnancy test, will be conducted prior to the acute phase, prior to the continuation phase, and at study termination. Physical examination and vital signs will be assessed at study entry and termination visits. Patient termination will occur if the patient experiences a worsening of MADRS scores greater than 30% above the baseline score in two successive visits or if MRS > 20 in two successive visits, or based on clinician judgment or patient preference.

1. Concomitant Medication and Therapy

All allowed concomitant medications will be unchanged throughout the study.

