SAE Definition: An SAE is any adverse event, without regard to causality, that is life-threatening or that results in any of the following outcomes: death; in-patient hospitalization or prolongation of existing hospitalization; persistent or significant disability or incapacity; or a congenital anomaly or birth defect. Any other medical event that, in the medical judgment of the Principal Investigator, may jeopardize the subject or may require medical or surgical intervention to prevent one of the outcomes listed above is also considered an SAE. A planned medical or surgical procedure is not, in itself, an SAE.

SAE Reporting Period: The SAEs that are subject to this reporting provision are those that occur from after the first dose of the Pfizer Product through 28 days after discontinuation of the Pfizer Product.

Follow-Up Information: Institution will assist Pfizer in investigating any SAE and will provide any follow-up information reasonably requested by Pfizer.

Regulatory Reporting: Reporting an SAE to Pfizer does not relieve Institution of responsibility for reporting it to the FDA, as required.

E. Publication and Presentation of Results

All data will be recorded, stored, and analyzed by the Duke and Tufts Medical Center sites. The co-PIs are solely responsible for ultimate presentation and publication of data produced by this study. The study enrollment and follow-up should be complete by the end of 2009. Study results will plan to be presented at the American Psychiatric Association meeting of 2009, and any other meetings as feasible. Publication of the main final manuscript will be planned for 2009. It is expected that two to three other manuscripts assessing secondary outcome measures will also be published by 2009.

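### The SAE reporting period outlasts every scheduled contact, so serious events after the last visit are captured only if the investigator happens to learn of them

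*Protocol*

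**What the plan says.** **Reporting period.** The Serious Adverse Event Reporting text in the Protocol (section XII.D) covers SAEs occurring after the first dose and "through 28 days after discontinuation of the Pfizer Product". It applies to subjects assigned to the Pfizer Product. The 24-hour reporting clock starts when the investigator first becomes aware of the event.

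**Scheduled contact.** Visit-Specific Treatment and Evaluation Sequence states: "Visits will be planned to occur at the screening visit and weeks 0, 1, 2, 3, 4, 5, 6". The Study Visit Schedule table has no column after Week 6, and the Study Design schematic runs from randomisation through 6 weeks to termination. On examinations the protocol says: "Physical examination and vital signs will be assessed at study entry and termination visits".

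**Drug after the blinded phase.** Blinding and Controls states: "All subjects will be offered the option of an open label courtesy trial of up to 8 weeks of treatment with ziprasidone". Potential Benefits repeats the 8-week maximum but gives non-completers a minimum of 2 months. Study Discontinuation/Termination says that subjects who do well receive Geodon and the others may choose it. Visit-Specific Treatment and Evaluation Sequence also places laboratory tests "prior to the continuation phase, and at study termination", although neither the schedule table nor the schematic shows a continuation phase.

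**The concern.** A reporting window defines which events count. It does not find them. Up to Week 6 the weekly visits do that, since adverse events are asked about at each one. After the last visit nothing in the protocol prompts anyone to ask, yet the protocol still declares the next 28 days reportable.

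The loss may well be uneven. Study Discontinuation/Termination removes patients for depressive worsening, a high mania score, persistent suicidal ideation, or deterioration that requires hospitalisation. In-patient hospitalisation is itself an SAE under the protocol's definition. Risks and Discomforts says that patients who worsen may be moved to routine care outside the study. These patients plausibly carry the higher risk in the following four weeks, while those who take open-label drug are more likely to stay in touch with the clinic. The late SAE record would then depend partly on who remained with the site.

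**Working it through.** No sample-size, power or alpha figure is involved, and the protocol gives no derived figure to reproduce. The check compares the last scheduled contact with the end of the reporting period.

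**Inputs**
- Blinded treatment: 6 weeks = 42 days (Study Design: "Patients will be randomized to ziprasidone or placebo in the 6 week acute phase of the study").
- Last scheduled visit: Week 6 = day 42, or the termination visit if earlier.
- Reporting tail: 28 days after discontinuation (section XII.D).
- Open-label option: "open label courtesy trial of up to 8 weeks of treatment with ziprasidone", so at most 56 days (Blinding and Controls).
- Assumption: drug stops on the day of the last visit, or of the last open-label dose.

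**Formulas**
- End of window = day of last ziprasidone dose + 28.
- Days without scheduled contact = end of window − day of last scheduled visit.

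**Case 1: ziprasidone completer, no open-label drug.** The window ends on day 42 + 28 = 70. Days without scheduled contact: 70 − 42 = 28. Share: 28/70 = 40%.

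**Case 2: ziprasidone patient stopped early on day D, no open-label drug.** The window ends on day D + 28, and all 28 post-treatment days have no scheduled contact. For example, a stop at Week 2 (D = 14) gives a window of 14 + 28 = 42 days, and 28/42 = 67%.

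**Case 3: full 8 weeks of open-label drug straight after Week 6.** Last dose: day 42 + 56 = 98. The window ends on day 98 + 28 = 126. Days after the last scheduled visit: 126 − 42 = 84, of which 56 are on drug. Share: 84/126 = 67%. This case holds only if courtesy drug counts as the Pfizer Product and there is no gap before it starts. For non-completers the end of the window cannot be fixed at all, because one statement gives a maximum of 8 weeks and another a minimum of 2 months.

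**Who has a window.** With 100 patients randomised 1:1, about 50 are assigned ziprasidone. A placebo patient who declines open-label drug never takes the Pfizer Product and has no window. The protocol breaks the blind only in a medical emergency, so a site cannot tell which blinded patients have a window and which do not.

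**The case against.** The strongest reply is that section XII.D is a duty to report known events, not a schedule of visits. A reporting window longer than the visit schedule is compatible with that duty. This is correct. A reader might infer that the protocol contradicts itself by ending safety follow-up at two different times; the documents do not support this, because the two passages govern different things. A reader might also infer that the last 28 days are never observed. That goes too far: any SAE the investigator learns of in that period must be reported.

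The second reply is that open-label drug is offered to every subject, and supplying it implies clinical contact. Contact is plausible, and so is some communication when a worsening patient is referred elsewhere. But no section specifies a visit, an examination or an SAE inquiry in that period. The 67% in Case 3 is therefore a share without *scheduled* contact, not without any contact. It also depends on whether courtesy drug given after study conclusion falls under the SAE provision, which the text does not settle.

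Third, a reader might infer that all 100 patients are affected. They are not: the provision covers subjects assigned to the Pfizer Product.

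Fourth, how SAEs are tabulated by period belongs in the statistical analysis plan, which is not at hand. That is accepted, and no finding is made on it. The schedule of contacts is different: it is protocol content, and this protocol sets it out visit by visit.

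**Conclusion.** The point holds as a gap in ascertainment. The protocol declares a period reportable and schedules nothing in it that would bring events to light. For a ziprasidone completer without open-label drug, 40% of the reportable period lacks scheduled contact; for an early leaver, the whole 28-day tail does. Both figures assume that drug stops on the day of the last visit. Any extension through open-label treatment is conditional on that drug counting as the Pfizer Product.

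How many SAEs would be missed cannot be computed, because the protocol gives no event rate. Selective loss among patients removed for worsening is a reasoned expectation, not a demonstrated figure. The primary MADRS comparison, alpha, power and sample size are untouched. This is a cheap improvement to safety reporting and does not threaten the trial's main conclusion.

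**What to change.** - Add one row to the Study Visit Schedule: a telephone SAE inquiry 28 days after the last dose of blinded or open-label study drug. It should cover every randomised patient, including early leavers, because the blind prevents sites from restricting it to those on ziprasidone.
- State in Visit-Specific Treatment and Evaluation Sequence and in the SAE Reporting Period text whether the open-label period falls under the SAE provision.
- Reconcile with that statement the passages on ziprasidone after the blinded phase: Blinding and Controls, the continuation phase mentioned in the visit sequence, Potential Benefits, and Study Discontinuation/Termination. Which length or arrangement applies is for the investigators to settle.

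Cost: about 100 telephone calls by existing coordinators (one per planned patient) and a short amendment.

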###### STUDY DESIGN

**Placebo**

6 weeks

6 weeks

**Ziprasidone**

**Parallel step**

Stratify by: Subtype of bipolar disorder (type I vs. type II/NOS, Presence of rapid cycling, Duration of current MDE (< vs. > 3 months)

**T**

**e**

**rm**

**i**

**n**

**a**

**t**

**i**

**o**

**n**

**R**

**a**

**n**

**d**

**om**

**i**

**z**

**a**

**t**

**i**

**o**

**n**

###### STUDY VISIT SCHEDULE

|  | **Screening** | **Weeks** | | | | | | | | | | | | | | | |
| --- | --- | --- | --- | --- | --- | --- | --- | --- | --- | --- | --- | --- | --- | --- | --- | --- | --- |
| **0** | **1** | | | **2** | | | **3** | | | **4** | | | **5** | | **6** |
| **VISITS:** | | | | | | | | | | | | | | | | | |
| Office Visits | • | • | • | | | • | | | • | | | • | | | • | | • |
| **PSYCHOMETRIC SCALES:** | | | | | | | | | | | | | | | | | |
| Demographics Form | • |  | |  | | |  | | |  | | |  | |  | |  |
| SCID Depression & Mania Modules | • |  | |  | | |  | | |  | | |  | |  | |  |
| Montgomery Asberg Depression Rating Scale (MADRS) | • | • | | • | | | • | | | • | | | • | | • | | • |
| Quick Inventory for Depressive Symptoms (QIDS) | • | • | | • | | | • | | | • | | | • | | • | | • |
| Mania Rating Scale (MRS) | • | • | | • | | | • | | | • | | | • | | • | | • |
| Hamilton Scale of Anxiety (HAM-A) |  | • | | • | | | • | | | • | | | • | | • | | • |
| Quality of Life Enjoyment and Satisfaction Questionnaire (Q-LES-Q) |  | • | | • | | | • | | | • | | | • | | • | | • |
| Scale to Assess Unawareness of Mental Disorder (SUMD) |  | • | | • | | | • | | | • | | | • | | • | | • |
| Drug Attitude Inventory (DAI) |  | • | | • | | | • | | | • | | | • | | • | | • |
| Clinical Global Impression Bipolar Depression (CGI-BP) |  | • | | • | | | • | | | • | | | • | | • | | • |
| Global Assessment of Function (GAF) |  | • | | • | | | • | | | • | | | • | | • | | • |
| LIFE-RIFT |  | • | | • | | | • | | | • | | | • | | • | | • |
| Systematic Assessment for Treatment Emergent Events |  | • | | • | | | • | | | • | | | • | | • | | • |
| Barnes Akathisia Scale (BAS) |  | • | | • | | | • | | | • | | | • | | • | | • |
| Simpson-Angus Scale for extrapyramidal symptoms (SAS) |  | • | | • | | | • | | | • | | | • | | • | | • |
| The structured Family History Screen (FHS) |  | • | |  | | |  | | |  | | |  | |  | |  |
| The Temperament and Affective Disorders Questionnaire (TEMPS-A) |  | • | |  | | |  | | |  | | |  | |  | |  |
| Side Effects Checklist |  | • | | • | | | • | | | • | | | • | | • | | • |
| Past Medication Response Structured Assessment |  | • | |  | | |  | | |  | | |  | |  | |  |
| PTSD Scale |  | • | |  | | |  | | |  | | |  | |  | |  |
| **MEDICAL ASSESSMENTS:** | | | | | | | | | | | | | | | | | |
| PE & Vital Signs |  | • | | |  | | |  | | |  | | |  | |  | • |
| Safety Labs | • |  | | |  | | |  | | |  | | |  | |  | • |

